APPENDIX L. THE TREATMENT SATISFACTION QUESTIONNAIRE (TSQ)^[[8]](#footnote-8)^

**PART A:**

Instructions: Using the scale shown in the box below, please rate ‘*how useful’* you found the various treatment components to be.

0 1 2 3 4 5 6 7

**Not at A little Somewhat Quite A lot Very much
 all so**

**Rating (0-7)**

| 1. How useful did you find the information on postpartum depression? | __________ |
| --- | --- |
| 1. How useful did you find the information regarding the available medical and psychological treatments for postpartum depression? | __________ |
| 1. How useful did you find learning about the causes of postpartum depression? | __________ |
| 1. How useful did you find developing your depression profile? | __________ |
| 1. How useful did you find the activity planning exercises? | __________ |
| 1. How useful did you find the problem solving exercises? | __________ |
| 1. How useful did you find the relaxation exercises (e.g., mindful breathing, visualization)? | __________ |
| 1. How useful did you find Cognitive Behaviour Therapy (CBT) for learning to change the way you think and feel? | __________ |
| 1. How useful did you find the thought diary for identifying unhelpful thinking styles? | __________ |
| 1. How useful was the five steps for problem solving (i.e., SOLVE)? | __________ |

**PART B:**

Instructions: Using the scale shown in the box below, please rate ‘*how much you personally liked’* the various treatment components.

0 1 2 3 4 5 6 7

**Not at A little Somewhat Quite A lot Very much**

**All So**

**Rating (0-7)**

| 1. How much did you personally like the information postpartum depression? | __________ |
| --- | --- |
| 1. How much did you personally like learning about the available medical and psychological treatments for postpartum depression? | __________ |
| 1. How much did you personally like learning about the causes of postpartum depression? | __________ |
| 1. How much did you personally like developing your depression profile? | __________ |
| 1. How much did you personally like the mood monitoring exercise? | __________ |
| 1. How much did you personally like the activity planning exercises? | __________ |
| 1. How much did you personally like the problem solving exercises? | __________ |
| 1. How much did you personally like the relaxation exercises (e.g., mindful breathing, visualization)? | __________ |
| 1. How much did you personally like Cognitive Behaviour Therapy (CBT) for learning to change the way you think and feel? | __________ |
| 1. How much did you personally like the thought diary for identifying unhelpful thinking styles? | __________ |
| 1. How much did you personally like using the five steps for problem solving (i.e., SOLVE)? | __________ |
| 1. How much did you personally like planning and engaging in social activities? | __________ |

**PART C:**

Instructions: Using the scale shown in the box below, please rate ‘*how much you think you improved’* with respect to your depression symptoms.

0 1 2 3 4 5 6 7

**Not at A little Somewhat Quite A lot Very much**

**all so**

**Rating (0-7)**

| 1. How much do you think you improved with respect to depression symptoms? | __________ |
| --- | --- |
| 1. How much do you think you improved with respect to the frequency of your depressed mood symptoms? | __________ |
| 1. How much do you think you improved with respect to the severity of your depressed mood? | __________ |
| 1. How much do you think you improved with respect to identifying your negative thoughts and feelings? | __________ |
| 1. How much do you think you improved with respect to your overall mood? | __________ |

**Part D:**

Instructions: Using the scale shown in the box below, please rate how *‘your life has changed’* in the various areas described below.

0 1 2 3 4 5 6 7

**Not at A little Somewhat Quite A lot Very much
 all so**

**Rating (0-7)**

| 1. How do you think your life has improved with respect to your participation in leisure activities? | __________ |
| --- | --- |
| 1. How do you think your life has improved with respect to your participation in family activities? | __________ |
| 1. How do you think your life has improved with respect to your participation in social activities? | __________ |
| 1. How do you think your life has improved with respect to your ability to be alone? | __________ |

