***Introduction***. Postpartum depression (PPD) and sub-clinical PPD affect approximately 8 to 15% of Canadian women following childbirth (Chalmers et al., 2008). The disorder is debilitating and impacts a woman’s quality of life and her ability to care for and connect with her infant. PPD is also related to short- and long-term consequences for the infant (Tronick & Reck, 2009). Unfortunately, PPD is undertreated for reasons including lack of access to providers and limited mobility. Using the internet to deliver therapy is an innovative way to improve access to psychological treatment. Evidence has suggested that internet cognitive behavior therapy (ICBT) results in significantly larger effect sizes compared to all other online interventions (Barak et al., 2008) and that therapist-assisted ICBT (TAICBT) is comparable to in-person CBT (Spek, 2007).While there is evidence to support the efficacy of TAICBT for the treatment of major depression (Cuijpers et al., 2010), to date, researchers have yet to determine whether this modality is efficacious for the treatment of PPD.

***Purpose and Hypotheses****.* The proposed study will determine whether TAICBT is more efficacious than a waitlist control (WLC) condition in reducing depressive symptom severity, anxiety, general stress, parental stress, and for improving quality of life for women with PPD. It is hypothesized that TAICBT participants will demonstrate significantly greater symptom and clinical improvement from pre- to post-treatment on all outcome measures. It is also expected that symptom improvements will be maintained four weeks following the conclusion of treatment. Given that the TAICBT has not been examined in PPD populations, treatment expectancy, satisfaction, and therapeutic alliance will also be investigated. It is hypothesized that: (a)TAICBT participants will report satisfaction with the treatment,(b) significant associations will be revealed between post-treatment therapeutic alliance ratings and symptom changes scores, and (c) treatment expectancy and satisfaction will be moderately correlated with symptom change scores on all outcome measures. To further understand the participants’ experience with TAICBT, ten open-ended questions will be asked.

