***Method****.* Using a randomized controlled design, 58 women will be randomized to receive either TAICBT treatment or assigned to a 7-10 week WLC. Participants assigned to the WLC will receive a pamphlet that includes information on information on PPD and websites for support services offered in Saskatchewan. The intervention will consist of a seven-module TAICBT program adapted for women afflicted with PPD. Each TAICBT participant will be assigned to a therapist who they can correspond with weekly via email. Potential participants will be screened using the **Edinburgh Postnatal Depression Scale** (EPDS; Cox et al., 1987), modules from the **MINI International Neuropsychiatric Interview** (Sheehan et al., 1998), as well as standard screening questions. If deemed eligible, the following additional outcome measures will be administered: (a)**Depression Anxiety Stress Scale- Short Form** (DASS; Lovibond & Lovibond, 1995) to measure levels of depression, stress, and anxiety; (b)**Parenting Stress Index- Short Form** (PSI-SF; Abidin, 1995) to assess stress in the parent-child system; (c) **World Health Organization Quality of Life – BREF** (WHOQOL-BREF; WHOQOL Group, 1998) to assess quality of life;(d) **Therapist Alliance Questionnaire** (TAQ; Kiropoulos et al., 2008, modified from Luborsky’s 1985 HAQ-II) to determine the degree to which participants perceive the relationship with their therapist as helpful; (e) **Treatment Satisfaction Questionnaire-Modified** (TSQ; Cox et al., 1994) to assess the client’s perceived satisfaction with treatment; and (f) **Credibility/Expectancy Questionnaire**(CEQ; Devilly & Borkovec, 2000) to measure credibility and treatment expectancy of the TAICBT treatment. The TAQ, TSQ, and CEQ will only be completed by those participants receiving TAICBT treatment. All other measures will be completed by both groups of participants at pre-treatment and post-treatment (10 weeks after baseline). Following the 7-10 week wait, participants in the WLC group will be contacted, re-screened, and if still eligible, they will be offered the treatment. At this time, the TAICBT participants will be asked to respond to ten open-ended questions regarding their experiences with the program. To provide a longer-term follow-up of depressive symptoms, TAICBT participants will be contacted by telephone four weeks following treatment completion and administered the EPDS and the depression module of the MINI.

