***TAICBT treatment***: Following completion of the baseline measures, the participants in the TAICBT condition will be provided with a login username and password to access Maternal Depression Online, which will be located at the following address: <http://www.onlinetherapyuser.ca>. As part of clinical practice, with client consent, a letter will be sent to the participant’s family physician informing them that their patient is participating in the Maternal Depression Online program (see Appendix N). This is done for two reasons. The first is to verify the client’s identity, and the second reason is to have a contact number in the unlikely case of an emergency. Upon initial login to the website, participants are provided with an information page and consent form (see Appendix G). The participants will then be offered the seven-module online treatment, with each module taking approximately one week to complete. Each module provides education about the disorder and assigns suggested exercises and homework to be completed in consort with an online therapist. The therapist communicates with their client once a week through emails that are contained within the Online Therapy USER website. Upon login for a new module, participants complete a weekly mood monitor (see Appendix O) and provide examples and answers questions from the previous module (see Introduction pages from http://www.onlinetherapyuser.ca/sitemap).

In order to assess change over time, following treatment completion, participants will be emailed the same website link to fluidsurvey.com to complete the post-treatment outcome measures along with measures related to therapeutic alliance (see Appendices H to M). The measures will take approximately 30-45 minutes to complete and will assess change in symptoms over the course of treatment. In addition to the measures, the participants will be asked to respond to a series of follow-up, open-ended questions regarding their experiences with the program (see Appendix P) as well as questions regarding any additional treatment they sought over the 10-week period (see Appendix O).

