**General Comments:**

1. What was the best part of the program? ________________________________________
2. What was the worst part of the program? ________________________________________
3. How could the program be improved? __________________________________________

Overall, how much improvement do you believe occurred, after completing the treatment program? (Please Circle)

| 0 1 2 3 4 5 6 7 8 9 10  **No Improvement Most Improvement**  **at All Possible** |
| --- |

1. How many hours did you spend in total reading and re-reading the content in the Maternal Depression Online Program?

Please circle one

1-5 hours 6-11 hours 12-17 hours 17-23 hours 24-29 hours 30 hours or Over

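### Three wording and answer-option defects in the satisfaction form (Appendix L) can blur the TSQ data behind hypotheses (a) and (c); minor, and confined to the TAICBT arm

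*Protocol*

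**What the plan says.** The Method summary gives the TSQ, in a modified version, to TAICBT participants only, "to assess the client’s perceived satisfaction with treatment". Under Purpose and Hypotheses it bears on two hypotheses: (a), that "TAICBT participants will report satisfaction with the treatment", and (c), that "treatment expectancy and satisfaction will be moderately correlated with symptom change scores on all outcome measures".

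The form in Appendix L contains:

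- **Part A (10 items) and Part B (12 items):** usefulness and liking of named components, each rated 0-7. A typical item is "How useful did you find the thought diary for identifying unhelpful thinking styles". No not-used or not-applicable answer is shown.
- **Part C (5 items):** amount of improvement in symptoms, 0-7.
- **Part D (4 items):** the instruction asks the woman to rate how "your life has changed". The items ask, for example, "How do you think your life has improved with respect to your participation in leisure activities". The 0-7 scale is one-sided.
- **Part E (2 items):** overall liking of the programme and enjoyment of contact with the therapist, 0-7.
- **General Comments:** free text, a 0-10 overall improvement rating, and total hours spent reading. The hours bands start at 1-5 and include "12-17 hours 17-23 hours".

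Section III, item 3 says that each module "assigns suggested exercises and homework to be completed in consort with an online therapist". Using every component is therefore not a condition of taking part.

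**The concern.** The TSQ is the satisfaction measure named in the protocol, so an answer with more than one meaning goes straight into the data for hypothesis (a) and the satisfaction part of (c). The three defects work differently.

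In Part D one experience, a worsened life, has two possible answers far apart on the scale, because instruction and items ask different questions. In Parts A and B a woman who did not use a component has no truthful answer. If she enters 0, she looks the same as a woman who used it and found it of no use or did not like it. In the hours item a woman who spent 17 hours has two correct answers, and one who spent less than an hour has none.

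An analysis plan can say how answers are scored. It cannot recover a distinction that the form did not collect.

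**Working it through.** The protocol states no TSQ score, cut-off or scoring rule, so there is no figure to reproduce. The check is a reading of each part against its answer options, followed by illustrations on assumed values.

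**Reading the form**

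| Part | What is asked | What has no clear answer |
|---|---|---|
| A (10 items), B (12 items) | usefulness, liking | component not used |
| D instruction | amount of change, no direction | direction of change |
| D items (4) | amount of improvement | worsening |
| Hours | total hours in bands | below 1 hour; 17 hours has two bands |

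The Part D mismatch lies within the form: the instruction and all four items differ on whether direction matters.

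**Illustration 1: non-use entered as 0.** Let m be the mean among users and u the share of women who did not use the component and entered 0. The recorded mean is (1 − u) × m + u × 0 = (1 − u) × m.

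| Users' mean m | u = 10% | 20% | 30% | 40% |
|---|---|---|---|---|
| 4 | 3.6 | 3.2 | 2.8 | 2.4 |
| 5 | 4.5 | 4.0 | 3.5 | 3.0 |
| 6 | 5.4 | 4.8 | 4.2 | 3.6 |

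For one woman who rates everything else 5 and enters 0 for k unused items, the Part A mean is 5 × (10 − k)/10 and the Part B mean is 5 × (12 − k)/12. With k = 1 these are 4.50 and 4.58; with k = 4 they are 3.00 and 3.33. If she leaves the items blank and blanks are left out of the mean, both stay at 5.

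**Illustration 2: worsening in Part D.** Suppose a share w of women worsened by 3 points and the rest improved by 4. The mean is (1 − w) × 4 − 3w if direction is kept, (1 − w) × 4 if worsening is entered as 0, and (1 − w) × 4 + 3w if every worsened woman rates the amount of change.

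| w | Direction kept | Entered as 0 | Entered as amount of change |
|---|---|---|---|
| 5% | 3.65 | 3.80 | 3.95 |
| 10% | 3.30 | 3.60 | 3.90 |
| 20% | 2.60 | 3.20 | 3.80 |

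The last column is an extreme, since it has every worsened woman follow the instruction and ignore the item in front of her.

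All values of m, u, w and the sizes of change are assumptions. The protocol gives none of them.

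**The case against.** Most of the counter-case stands, and it limits the point.

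- **No scoring rule.** A reader might infer that non-use is scored as dislike. The protocol does not say so. A blank is possible: the alliance questionnaire in Appendix K tells the woman to rate every item, but the TSQ does not. In Part A a 0 means not useful, and in Part B it means absence of liking.
- **Timing.** A reader might infer that the TSQ is taken at 10 weeks whether or not the modules are finished. The 10-week clause in the Method summary covers the measures other than the TAQ, TSQ and CEQ. Section III, item 3 sends the post-treatment forms after treatment is completed. It is tempting to argue that early stoppers who enter zeros would create the correlation predicted in (c). That argument needs non-finishers who return the form, zeros for everything they missed, and a satisfaction score built from the 22 component items. The protocol states none of these.
- **Direct satisfaction items exist.** The two Part E items serve hypothesis (a) and do not depend on which components were used.
- **Worsening is measured elsewhere.** The pre/post symptom and quality-of-life scales, the free-text question on the worst part of the programme, and Appendix P can all show it. Every Part D item says improved, so a high entry for worsening is unlikely.
- **Some of this is preference.** One-sided improvement scales in Part C and the overall rating are a choice, not an error. The hours item is named in no hypothesis or analysis.

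The form defects themselves remain. The other sources do not show what a particular 0, blank or high number on the TSQ meant.

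**Conclusion.** The point holds as a minor one. Part D's instruction and items disagree, Parts A and B have no answer for an unused component although exercises are only suggested, and the hours bands overlap at 17 and leave out use below 1 hour. These defects can blur hypothesis (a) and the satisfaction part of (c), in the TAICBT arm only. They do not touch the between-arm efficacy comparison.

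The size is unknown. The illustrations show that zeros for non-use would lower a component mean in proportion to the non-use share, and that worsening entered as 0 or as an amount of change would raise the Part D mean. How often either would happen cannot be derived from the protocol. The case for acting rests on the low cost of the edits and on the fact that an ambiguous answer cannot be clarified from the form once it is submitted.

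**What to change.** 1. **Part D:** make the instruction and the items ask the same question. Either reword the instruction to ask about improvement, or put both on a single scale running from worse through no change to better.
2. **Parts A and B:** add a did-not-use answer to all 22 items, leave it out of the item means, and report how often it is chosen for each item. The report is needed because women may skip components they dislike. Excluding them would then make a component look better than it was.
3. **Hours:** print the bands as less than 1, 1-5, 6-11, 12-17, 18-23, 24-29, and 30 or over.

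The cost is a few edits to an online survey form. The downside is a further departure from the source questionnaire, which the study has already modified. Part C and the overall improvement rating need no change on these grounds.

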**Part E:**

Instructions: Using the scale provided, please rate the following treatment evaluation questions.

0 1 2 3 4 5 6 7

**Not at A little Somewhat Quite A lot Very much
 all so**

**Rating (0-7)**

1. How much did you like the treatment program? ___________
2. How much did you enjoy communicating with your therapist? ___________

**General Comments:**

1. What was the best part of the program? ________________________________________
2. What was the worst part of the program? ________________________________________
3. How could the program be improved? __________________________________________

Overall, how much improvement do you believe occurred, after completing the treatment program? (Please Circle)

| 0 1 2 3 4 5 6 7 8 9 10  **No Improvement Most Improvement**  **at All Possible** |
| --- |

1. How many hours did you spend in total reading and re-reading the content in the Maternal Depression Online Program?

Please circle one

1-5 hours 6-11 hours 12-17 hours 17-23 hours 24-29 hours 30 hours or Over

APPENDIX M. CREDIBILITY/EXPECTANCY QUESTIONNAIRE (CEQ)^[[9]](#footnote-9)^

We would like you to indicate below how much you believe, *right now*, that the therapy you are receiving will help to reduce your anxiety. Belief usually has two aspects to it: (1) what one *thinks* will happen and (2) what one *feels* will happen. Sometimes these are similar; sometimes they are different. Please answer the questions below. In the first set, answer in terms of what you *think*. In the second set answer in terms of what you really and truly *feel*. Your therapist will not see these ratings.

**Set I**

1. At this point, how logical does the therapy offered to you seem?

| 1 | 2 | 3 | 4 | 5 | 6 | 7 | 8 | 9 |
| --- | --- | --- | --- | --- | --- | --- | --- | --- |

not at all logical somewhat logical very logical

1. At this point, how successfully do you think this treatment will be in reducing your depressive symptoms?

| 1 | 2 | 3 | 4 | 5 | 6 | 7 | 8 | 9 |
| --- | --- | --- | --- | --- | --- | --- | --- | --- |

not at all useful somewhat useful very useful

1. How confident would you be in recommending this treatment to a friend who experiences similar problems?

| 1 | 2 | 3 | 4 | 5 | 6 | 7 | 8 | 9 |
| --- | --- | --- | --- | --- | --- | --- | --- | --- |

not at all confident somewhat confident very confident

4. By the end of the therapy period, how much improvement in your depressive symptoms do you think will occur?

| 0% | 10% | 20% | 30% | 40% | 50% | 60% | 70% | 80% | 90% | 100% |
| --- | --- | --- | --- | --- | --- | --- | --- | --- | --- | --- |

**Set II**

For this set, close your eyes for a few moments, and try to identify what you really *feel* about the therapy and its likely success. Then answer the following questions.

1. At this point, how much do you really *feel* that therapy will help you to reduce your depressive symptoms?

| 1 | 2 | 3 | 4 | 5 | 6 | 7 | 8 | 9 |
| --- | --- | --- | --- | --- | --- | --- | --- | --- |

not at all somewhat very much

1. By the end of the therapy period, how much improvement in your depressive symptoms do you really *feel* will occur

| 0% | 10% | 20% | 30% | 40% | 50% | 60% | 70% | 80% | 90% | 100% |
| --- | --- | --- | --- | --- | --- | --- | --- | --- | --- | --- |

Appendix N.Physician Notification Form

**Online Therapy USER (Unit for Service Education and Research)**
[name]
Department of Psychology
University of Regina
[name]
[name]

Date: ___________________________________

Doctor Name: ___________________________________
Clinic Name: ___________________________________
Address: ___________________________________
 ___________________________________
 ___________________________________

RE: Notification of client participation in the Online Therapy USER Program

Dear Dr. ______________________________:

I am writing to inform you that your patient _____________________(health card #____________________ )
(DOB mm/dd/yyyy: _________________________) is a participant in the Online Therapy USER Program and has provided your name as a contact in case of emergency.

The Online Therapy Unit is a new online mental health unit that allows trained therapists to provide Online Cognitive Behavior Therapy (Online-CBT) to residents of Southern Saskatchewan who have difficulties with postpartum depression, major depression, generalized anxiety, and/or panic. Online-CBT involves helping clients learn how to identify and make changes to problematic thoughts (cognitions) and actions (behaviours). Clients who are screened to be appropriate for this service review educational material online and correspond with their therapist over a secure e-mail system. Online-CBT has been found to be effective and has many advantages including being more available, convenient and efficient than CBT delivered in person. If you are interested you can review our website at [www.onlinetherapyuser.ca](http://www.onlinetherapyuser.ca)

If you have any concerns about this patient participating in treatment, please call us. Reasons for non-participation might include:

1) the patient is not 18 years of age
2) the patient is at risk of suicide
3) the patient suffers from problems with alcohol or drugs
4) the patient suffers from psychotic symptoms

If you have any questions, please call the Online Therapy Unit at [contact] or contact [name] at [contact].

Sincerely,

[name]

